| 1. **Study Design**   For this study, we will use a retrospective cohort study design, looking at patients with consultations for infection and/or antibiotic prescribing between 1st April 2007 and 31st December 2015. (for an exact definition see *K. Study population* and *Error: Reference source not found*)  In a first step (Objective 1), we will describe the incidence of GP consultations for infection and the incidence of antibiotic prescribing in the main study population. This will provide important context on the burden of infection and frequency of antibiotic use in primary care.  Within the main study population, we will then undertake a nested cross-sectional study looking at all antibiotic prescriptions in the main study population. For each prescription we will use Read codes on the day of the prescription to establish the reason for the prescription. (Objective 2) This will inform our understanding of why antibiotics are prescribed.  Next, we will undertake a series of cohort studies focused on specific infectious syndromes within the main population. Three nested cohorts will be built based on a GP consultation for a) respiratory tract infection, b) urinary tract infection and c) skin/soft tissue infection. For each cohort, we will estimate the rate of infection-related adverse outcomes within 28 days of the initial GP consultation for patients with and without antibiotic treatment. (Objective 3)  In order to determine the protective effects of antibiotics against these adverse outcomes, we will then estimate the Number Needed To Treat with antibiotics (NNT) to prevent one additional adverse outcome. In particular, we will compare the NNT for patients with and without co-morbidities of interest, obesity or smoking. (Objective 4).  Finally, we will synthesize out analyses in objectives 1-4 to develop a risk model for each cohort (respiratory, urinary and skin/soft tissue models). These models will support clinical decisions and patient communication around the need for antibiotic treatment for suspected infection (Objective 5).  Results across all steps will be stratified or adjusted by age, gender, SES, ethnicity, co-morbidity, obesity and smoking status. |

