| 1. **Sample size considerations**   The main effects of interest in this study are the protective effect of antibiotic treatment (ORAB) and how this effect differs by co-morbidity (ORCO; i.e. the interaction between antibiotic treatment and co-morbidity).  Below, we derive sample sizes needed to detect these effects at 5% significance and 80% power (see Appendix Sample Size Calculation for detailed information on calculations and assumptions). We do so first for COPD patients with a respiratory infection based on previously published effect sizes. We will then relate these sample sizes to patients with other co-morbidities and with urinary or skin/soft tissue infections.  **Respiratory infections**  The power to detect any protective effects depends heavily on the risk of developing the outcome in question.  Past studies looked at a range of individual outcomes, including some extremely rare outcomes with risks as low as 0.04% (e.g. mastoiditis after URTI). They found average effect of antibiotics of ORAB = 0.69.11 and a sample size of ***971,057*** is required to detect this effect in our study.12 To be able to further investigate interactions, i.e. is the protective effect of antibiotics against rare outcomes such as mastoiditis different in patients with COPD versus no COPD, a sample size of **approx. 14 million** patients would be required.13 This is beyond the scope of this study.  Within this study, we will not consider effect sizes in rare outcomes such as mastoiditis individually. Instead, we will look at composite outcomes relevant to patients who consulted for infections, i.e. outcomes such as re-consultations, hospitalisations, etc. (see M. Exposures, Health Outcomes§ and Covariates for details). The risk for these outcomes is much more likely to be around 2.4% previously found for pneumonia.11 For this risk, required sample sizes for the protective effect of antibiotic treatment (ORAB) and how this effect differs by co-morbidity (ORCO) reduce to ***16,512***and ***258,247***.  Assuming a total sample size of at least 3,355,353 found previously (based on only 162 practices11), this study will be powered to detect ORAB and ORCO as small as 0.975 and 0.83, i.e. we will have the power to detect a protective effect of antibiotics against adverse outcomes as small as 2.5% and an increase in effects of antibiotics by 17% points in co-morbid patients.  **Urinary tract and skin/ soft tissue infections**  There are roughly 1/5 as many cases of urinary tract infection and 2/5 as many cases of skin/soft tissue infections as compared to respiratory infections.14 This translates into 671,070 cases of urinary and 1,342,141 cases of skin/ soft tissue infection. No published figures on effect sizes in urinary or skin infections could be found. Assuming similar effect sizes as in respiratory infections, the numbers for both kinds of infection well exceed the minimum sample size of 258,247 needed.  **Other comorbidities**  The powers to detect the same effects for diabetes, CKD, asthma, smoking and obesity are expected to be the same or higher, given the higher prevalence for these conditions (H. Feasibility counts). |

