| 1. **Data/ Statistical Analysis**   *1. Estimate the incidence of i) GP consultations for infection and ii) antibiotic prescriptions*  For every patient in cohort 1, data on all consultations for infection and antibiotic prescriptions occurring within the study period will be extracted. We will estimate the incidence of GP consultations for infection and antibiotic prescriptions. This will be done for all consultations and prescriptions, and then separately for each category of infection and each class of antibiotics, based on chapter 5.1 of the British National Formulary (BNF) (see Appendix Tables 1 & 2). The denominator will be estimated as total person-time contributed by patients in the cohort during the study period. We will use Poisson regression to estimate the adjusted rate of consultation and prescription, taking account of the effect of age, gender, SES, ethnicity, selected co-morbidity, smoking and obesity. Random effects will be included to take account of clustering of observations by practice. Rates will be assessed for overdispersion by additionally fitting a negative binomial model and testing for alpha greater than zero via a likelihood-ratio test. If rates are found to be overdispersed, the negative binomial model will be used instead of a Poisson model. Adjusted rate ratios will be presented with 95%-confidence intervals.  *2. Describe antibiotic prescribing patterns linked to the reason for prescription*  The overall number of antibiotic prescribing episodes will be calculated for each patient individually, counting all recorded prescriptions between 1st April 2007 and 31st December 2015. For each episode, a clinical indication will be ascertained. Read codes for a diagnosis or symptom of infection recorded on the same day as the antibiotic prescription will be assumed to represent an indication for the prescription. Where more than one possible indication within the same type of infection is recorded on the day of prescription, the more granular code will be used. If multiple indications across different types of infection are recorded, the prescription will be labelled as having multiple indications. Conversely, if no infectious indication for a prescription was found, the prescription will be labelled as having no infectious indication and we will look for any non-infectious codes associated with the date of antibiotic prescription. The ten most common indications will be established and compared to the same numbers for the period from 1998-2001.14 This approach will be replicated for each class of antibiotics based on chapter 5.1 of the BNF. Patterns of repeat consultation or prescription during episodes of infection which may be prolonged will be investigated for each antibiotic prescription extracted in objective 1. We will define a new episode as a consultation or prescription recorded at least 28 days after any previous consultation for infection or antibiotic prescription. We will undertake sensitivity analyses to investigate the impact of using different time periods to define an episode. We will also examine the use of regular (prophylactic) antibiotic treatment.  Proportions and appropriate 95%-confidence intervals will be calculated and all results will be stratified by age-group, gender, SES, ethnicity, selected co-morbidity, obesity and smoking status. Descriptive data will be displayed graphically.  *3. Estimate the incidence of adverse outcomes in the following 28 days*  For each of the selected clinical infection syndromes in the nested cohort study, events in CPRD, HES and ONS will be searched for all adverse outcomes of interest (see *M.* Exposures, Health Outcomes§ and Covariates). Crude incidence rates of for each outcome will be calculated for patients who were treated (exposed) and not treated (unexposed) with an antibiotic. The denominator will be estimated as the total person-time contributed by patients at risk of each adverse outcome, taking account of the fact that this will be different for each outcome. For example, exposed and unexposed patients cannot consult General Practice if they have been admitted to hospital and should therefore not contribute to the denominator during this period when estimating rates of GP re-consultation in the 28 days following consultation for infection. A Poisson regression model will be used to estimate adjusted rates of adverse outcomes in each group, controlling for age, gender, socio-economic status, ethnicity, co-morbidity, obesity and smoking status and assessing for interaction between age and co-morbidity. Random effects will be included to take account of clustering of observations by practice. If the outcomes are overdispersed, negative binomial models will be used instead of Poisson models. Adjusted rate ratios will be presented with 95%-confidence intervals.  *4. Estimate the number of patients needed to treat with antibiotics to avoid one infection-related adverse outcome*  For each clinical infection syndrome-related adverse outcome identified in objective 3, the odds of that outcome in the 28 days following consultation for those treated with antibiotics (unexposed) and not treated with antibiotics (exposed) will be estimated using logistic regression. We will calculate adjusted odds ratios for the protective effect of antibiotics, adjusting for age, gender, SES, ethnicity, year/season, co-morbidity and the probability of receiving antibiotic treatment (see *O. Plan for addressing confounding*) and assessing for interactions with age and co-morbidity. We will use mixed models to adjust for clustering at a practice level and to take account of clustering of observations within a patient due to repeat episodes of infection. Where there is a significant effect of antibiotics between treated and untreated patients, the NNT or NNH to prevent one individual from developing an adverse outcome is calculated as *1/(absolute risk difference)*. A significant effect will be defined by a p-value < 0.05 for the coefficients of antibiotic treatment and its interactions. To avoid an arbitrary cut-off point, p-values close to 0.05 will also be assessed but discussed separately. The NNT will then be used to assess the clinical relevance of any significant differences found. Whilst the relative risk reduction (RRR) may be similar, the NNT may be different due to differing background risk. This will be explored.  *5. Develop risk prediction tools to support clinical decision making*  For each cohort (i.e. for each of the clinical syndromes of UTI, RTI and SSTI), we will develop a logistic regression risk model to predict the risk of adverse outcomes if patients are treated versus not treated with antibiotics. Models will be developed on a random sample of 80% of the observations within a cohort, reserving 20% of the data to estimate the model’s predictive performance.  A negative outcome will be defined as the occurrence of any of the following within 28 days following the index consultation: hospital admission for infection or complication; re-consultation for infection; A&E admission; death. Antibiotic treatment will be defined as a prescription of an antibiotic on the day of consultation for clinical syndrome. Risk factors will be selected based on the analyses outlined in objectives 1-4 and broadly grouped into: socio-demographic variables, co-morbidity and clinical presentation. Biologically plausible interactions between risk factors and age and between risk factors and co-morbidities will be examined.  Whereas age and sex will be forced into the model, other risk factors will be added in order of their significance in objective 4. Risk factors will be kept in the model if they improve the predictive performance of the model as defined by model discrimination and model calibration.17 For example, a risk factor will be used in the model if it improves discrimination and/or calibration. If a variable improves discrimination but reduces calibration, it will still be included in the model, but will be omitted if it increases calibration at the cost of discrimination.  Model discrimination, i.e. the model’s ability to correctly identify patients with and without an outcome, will be estimated using the concordance (c) statistic.18 The c statistic represents the probability that between two randomly chosen patients, one with the outcome and one without, the model assigns a higher score to the patient with the outcome. As a second measure, model calibration will be assessed using the Hosmer-Lemeshow test.18 We will additionally assess model calibration graphically for reasons for poor calibration by comparing the mean observed outcome in deciles of predicted risk. In this calibration plot, the intercept indicates the extent to which predictions are systematically too low or too high, while the slope reflects overfitting of the model.  For each model, we will estimate the internal validity of discrimination and calibration estimates using cross-validation with bootstrap subsampling based on 1000 iterations. In a secondary analysis, we will assess model performance in subgroups by age, sex and co-morbidity.  Finally, we will develop a simplified scoring system using the risk factors in the model,17 assigning the total score to a specific absolute risk of adverse outcomes in the 28 days following consultation, comparing outcomes if an individual is treated versus not treated with antibiotics. We will assess the predictive performance of the risk scores using the approaches outlined above. |

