| 1. **Plan for addressing confounding**   In objectives 1-3 the aim is to describe rates and undertake descriptive analyses rather than to make inferences about the effect of antibiotic treatment, which is the purpose of objectives 4 and 5. For this reason the issue of confounding is only relevant to objectives 4 and 5.  Individuals who are at higher risk of complications will be more likely to be prescribed antibiotics by their GP (i.e. confounding by indication), introducing a systematic difference between those who are treated and not treated with antibiotics. In this scenario, untreated cases will be less likely to experience adverse events irrespective of their exposure to antibiotics, tending to underestimate the protective effect of antibiotics. We will use propensity score methods to attempt to adjust for this issue. These methods are increasingly used to mitigate the consequences of non-random allocation of treatment in observational studies by modelling the a priori probability of each patient to receive the treatment.  We will use the treatment propensity scores to perform an inverse probability of treatment weighting to account for baseline differences in treated and untreated participants. This will enable assessment of absolute risk and numbers needed to treat to prevent re-consultation and hospitalisation in different groups.19 Propensity score weighting in effect produces a synthetic sample in which the distribution of measured baseline covariates is independent of treatment assignment. Presentation and analyses of results are very similar to a randomized trial allowing assessment of absolute risk and numbers needed to treat in different groups.  In order to create appropriate propensity scores, we will attempt to capture indicators for severity of disease and patients’ risk of complication, such as prior hospitalisation and immunosuppression. Measures such as vital signs are usually poorly recorded which can hamper efforts to estimate disease severity. To overcome this issue we will use GP prescribing preference as an instrumental variables, as described by Davies et al 2013.20  Besides confounding by indication, a number of further factors might influence prescribing. The decision to prescribe an antibiotic is a complex process, depending on multiple characteristics on the patient and practice level. Patients’ demographic factors, patients’ attitude towards antibiotic prescribing, physicians’ workload, date of consultation and geographic location of the practice have been found to influence physicians’ prescribing decisions.21 The use of further instrumental variables may help to estimate the impact of these factors in our analysis and we will also control for differences in prescribing habits between practices through the application of random effects models taking account of potential correlation within multiple episodes of the same patient and between patients within the same practice.  Acknowledging that differences in practice prescribing do not necessarily constitute actually differing prescribing habits but might instead reflect underlying differences in coding, we will undertake an exploratory analysis to look at variation between practices graphically. Using a novel approach we will visualise variability between multiple data-generating sources (i.e. practices) that was specifically designed and tested for multitype, multivariate and multimodal biomedical data.22,23 Where outlying practices are identified, analysis will be re-run without those practices and results presented with the analysis outlined in *N. Data/ Statistical Analysis*. |

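### Objective 4 does not require the type of infection presented in the propensity weights or the outcome model, although it is coded and is a plausible confounder by indication

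*Protocol*

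**What the plan says.** Section G (Study Design) sets the level of pooling: "Three nested cohorts will be built based on a GP consultation for a) respiratory tract infection, b) urinary tract infection and c) skin/soft tissue infection". Section K (Study population) lets a patient enter on the day of the infection consultation, and section M refers to code lists for the three syndromes. Every episode in these cohorts, treated or not, therefore enters through an infection code.

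Section N, step 4, fits a logistic model for each outcome, "adjusting for age, gender, SES, ethnicity, year/season, co-morbidity and the probability of receiving antibiotic treatment" and "assessing for interactions with age and co-morbidity". The section M covariate list holds demographics, deprivation, chronic conditions, obesity, smoking, season and year. The Amendments section adds further chronic conditions, immunosuppression and a co-morbidity index. Neither list names the type of infection within a syndrome.

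For the weights, section O states: "we will attempt to capture indicators for severity of disease and patients’ risk of complication, such as prior hospitalisation and immunosuppression". It adds GP prescribing preference as an instrument because vital signs are poorly recorded. Step 5 names clinical presentation as a group of predictors for the risk models; steps 3 and 4 do not.

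**The concern.** Sections O and S (Limitations) treat confounding by severity as the main threat to the antibiotic effect. The kind of infection a patient presents with plausibly affects both the decision to prescribe and the 28-day outcome. Inverse probability weighting balances only the covariates put into the score. If infection type is left out, treated episodes may hold a larger share of serious infections than untreated ones, and the pooled OR moves towards or past 1.

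Section I gives the difference in antibiotic effect by co-morbidity as a main effect of interest, and step 4 turns it into NNTs that inform prescribing tools. If the infection mix differs between patients with and without a co-morbidity, a difference in mix could be read as a difference in antibiotic benefit.

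**Working it through.** **1. The plan's own figure.** For a binary exposure in logistic regression,

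N = (z₀.₉₇₅ + z₀.₈₀)² × [1/((1−t)·p₀(1−p₀)) + 1/(t·p₁(1−p₁))] / (ln OR)²,

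where t is the treated share, p₀ the untreated risk and p₁ the risk implied by the OR. Section I gives OR 0.69 and p₀ = 2.4%, so p₁ = 1.668%. The protocol does not state t. With t = 80%, N = 16,512, as stated; at p₀ = 0.04%, N = 971,057, as stated; and the detectable OR at 3,355,353 is 0.975, as stated. The sample size arithmetic is therefore not in question. About 80% treated is a share consistent with the plan's figures, but it remains an inference.

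**2. Where infection type could enter objective 4.**

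| Place | Infection type named? |
|---|---|
| Section M covariates | No |
| Step 4 adjustment set | No |
| Step 4 interactions | No (age and co-morbidity) |
| Section O propensity inputs | Not among the examples; wording open |
| Amendment covariates | No |

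**3. Illustration of size.** Take two infection types in one syndrome, with the same true OR of 0.69 (section I) in each. Assumed: the share of serious episodes s, untreated risks r_m and r_s, and treated shares t_m and t_s. The value 2.4% for r_s is borrowed from section I, where it is the risk of an outcome; its use here for a subtype is an assumption.

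- Treated risk in each type: odds = 0.69 × r/(1−r), converted back to a risk.
- Pooled treated risk: the types weighted by (1−s)t_m and s·t_s.
- Pooled untreated risk: the types weighted by (1−s)(1−t_m) and s(1−t_s).
- Standardised NNT: 1/(risk difference) with both arms given the whole mix.

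Worked case: s = 20%, risks 1.2% and 2.4%, treated 78% and 85%. Treated risks by type are 0.831% and 1.668%.

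- Pooled treated: (0.624 × 0.831% + 0.170 × 1.668%)/0.794 = 1.010%.
- Pooled untreated: (0.176 × 1.2% + 0.030 × 2.4%)/0.206 = 1.375%.
- Pooled OR = 0.73; NNT = 1/0.003644 = 274.
- Standardised: 1.440% − 0.999% gives NNT 227.

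| s | Untreated risk, mild/serious | Treated, mild/serious | Treated overall | Pooled OR | Pooled NNT | Standardised NNT |
|---|---|---|---|---|---|---|
| 20% | 1.2%/2.4% | 80%/80% | 80% | 0.69 | 227 | 227 |
| 20% | 1.2%/2.4% | 78%/85% | 79% | 0.73 | 274 | 227 |
| 20% | 1.2%/2.4% | 50%/70% | 54% | 0.77 | 324 | 227 |
| 20% | 1.0%/2.4% | 50%/80% | 56% | 0.86 | 640 | 255 |
| 20% | 0.5%/2.4% | 40%/85% | 49% | 1.32 | apparent harm | 371 |
| 30% | 0.5%/2.4% | 40%/85% | 53.5% | 1.43 | apparent harm | 305 |

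**4. The co-morbidity contrast.** Assume s = 20% without and 40% with the co-morbidity, and risks of 1.2% and 2.4%.

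| Treated, mild/serious | Pooled OR, without/with | Pooled NNT, without/with | Standardised to own mix |
|---|---|---|---|
| 80%/80% | 0.69/0.69 | 227/195 | 227/195 |
| 78%/85% | 0.73/0.75 | 274/255 | 227/195 |
| 75%/90% | 0.78/0.83 | 351/401 | 227/195 |

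In the first row the NNTs differ only because background risk differs, and nothing is biased. In the last row the order of the two NNTs reverses, and the ratio of ORs is 1.06 when the truth is 1.

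These are crude figures, with no weighting, other covariates or instrument applied.

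**The case against.** **The severity wording is open.** Section O introduces prior hospitalisation and immunosuppression as examples, so the score may include infection type, and exact propensity inputs are often left to the analysis plan. This stands: a reader might infer that the plan never adjusts for infection type, and the text does not support that. It remains true that both examples describe patient history, and that the adjustment set and covariate lists that are written out omit the variable.

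**An instrument is planned.** GP preference is aimed at unrecorded severity and may reduce confounding of the overall effect. The protocol does not say how it combines with the weighted step 4 model, and it would not by itself separate infection mix from co-morbidity.

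**Section I does not show that subtypes differ in risk.** It mentions "extremely rare outcomes with risks as low as 0.04% (e.g. mastoiditis after URTI") and 2.4% for pneumonia. It is tempting to read these as the spread of risk between mild and serious presentations. Both are risks of an outcome, and the outcomes differ. The objection stands in full.

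**The step 2 code rule covers prescriptions only.** Its instruction that "the more granular code will be used" applies to codes on the day of a prescription, so it does not classify untreated episodes. This also stands; the usable source is the code that defines cohort entry.

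**An NNT difference from background risk is real.** Step 4 says that differing background risk will be explored. The equal-treatment row above agrees: such a difference is not bias, though the plan names no means of telling it apart from a difference in antibiotic effect.

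**Conclusion.** The point holds for objective 4, as a worthwhile and cheap reduction of bias. A recorded, plausibly strong confounder by indication is permitted by the plan but not required in the weights or the outcome model.

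The size cannot be fixed from the protocol. With roughly 80% treated and a small imbalance between types, the illustration moves the OR from 0.69 to 0.73 and the NNT from 227 to 274. That is a shift of about 6% in the OR (0.732/0.69 = 1.06), larger than the 2.5% effect that section I says can be detected, so sample size alone would not remove a bias of that order. A reader might infer that antibiotics will look harmful. That result needs the assumed 40%/85% treatment split together with a mild risk of 0.5%, and the documents support neither.

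Objective 3 is outside the point. It adjusts by "controlling for age, gender, socio-economic status, ethnicity, co-morbidity, obesity and smoking status and assessing for interaction between age and co-morbidity", but section O declares objectives 1 to 3 descriptive.

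**What to change.** - Group the Read codes of the index consultation, which define cohort entry (Appendix Tables 2 and 3), into pre-set subtypes within each syndrome, with an unspecified category. Apply the grouping to treated and untreated episodes alike.
- Add subtype to the section M covariates, the propensity model and the step 4 outcome model.
- Check balance on subtype after weighting and report it.
- Keep the overall NNT by co-morbidity. Supplement it with NNT by subtype, or standardised to a common subtype mix, so that case mix can be told apart from a difference in antibiotic benefit.

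The cost is a few lines of text and a grouping of code lists that the plan already refers to; those lists are separate files not shown here, so how finely they divide is not known. The drawback is that some episodes carry only non-specific codes and that coding varies between practices, as section S (Limitations) acknowledges. Adjustment for subtype will therefore be partial. Objective 3 needs no change.

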| 1. **Study Type**   First we will **describe** the incidence of and relationships between antibiotic prescribing, GP consultation for infection and infection related adverse outcomes for all patients and for subgroups of patients based on risk factors including: age, gender, SES, co-morbidity, smoking status and obesity.  Next we will then **test the hypothesis** that the protective effect of antibiotics against adverse outcomes of infection differs between groups of patients with and without these risk factors.  Finally, we will use our results to inform the **methodological** development of risk prediction models to support clinical decisions around antibiotic treatment. |

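### The Objective 4 model names neither obesity nor smoking status, although the protocol promises NNT comparisons and a test of effect modification by both

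*Protocol*

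**What the plan says.** Section N (Data/Statistical Analysis), step 4 specifies a logistic model for each adverse outcome in each infection syndrome, "adjusting for age, gender, SES, ethnicity, year/season, co-morbidity and the probability of receiving antibiotic treatment" and "assessing for interactions with age and co-morbidity". An NNT is calculated where the antibiotic effect is significant, and the rule is: "A significant effect will be defined by a p-value < 0.05 for the coefficients of antibiotic treatment and its interactions".

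Other parts of the protocol expect more of Objective 4:

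- Study Design: "In particular, we will compare the NNT for patients with and without co-morbidities of interest, obesity or smoking".
- Study Type lists smoking status and obesity among the risk factors. It then sets out to test the hypothesis "that the protective effect of antibiotics against adverse outcomes of infection differs between groups of patients with and without these risk factors".
- Objectives, Specific Aims and Rationale says that the NNT will account for obesity and smoking status as well as co-morbidity.
- Sample size considerations, after defining the treatment-by-co-morbidity interaction as a main effect of interest: "The powers to detect the same effects for diabetes, CKD, asthma, smoking and obesity are expected to be the same or higher".

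Within section N, step 3 fits its Poisson model "controlling for age, gender, socio-economic status, ethnicity, co-morbidity, obesity and smoking status". Steps 1 and 2 also name obesity and smoking in addition to co-morbidity.

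**The concern.** Step 4 is the only one of the first four analysis steps that drops obesity and smoking, and it is the step meant to answer the question about them. The section on confounding says that confounding matters only for Objectives 4 and 5, so the shorter list falls in the step where adjustment counts most.

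Three things are at stake:

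1. The hypothesis in Study Type goes untested for two of its named risk factors.
2. The p < 0.05 rule on interactions has nothing to act on for those factors.
3. Step 5 adds risk factors, other than age and sex, in order of their significance in Objective 4. A factor that was not in the Objective 4 model has no place in that order.

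The two groups are not marginal. Study Background singles out obesity as a condition where the reason for greater antibiotic use is less clear. Feasibility counts gives, from an earlier study in another database, 395,825 smokers and 358,930 obese patients. The other groups are 216,379 with asthma, 107,382 with diabetes, 79,056 with CKD and 36,119 with COPD. These figures show the size of the groups. They do not measure any bias.

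**Working it through.** **Comparing the lists.** Most of the check is textual.

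| Place in protocol | Obesity and smoking named? | Apart from co-morbidity? |
|---|---|---|
| Section N, steps 1 to 3 | Yes | Yes |
| Section N, step 4, adjustment | No | – |
| Section N, step 4, interactions | No | – |
| Section M, covariates | Yes | Yes; co-morbidities are diabetes, CKD, COPD, asthma |
| Study Design, NNT comparison | Yes | Yes |
| Rationale, NNT | Yes | Yes |
| Aim 3 | Yes | No, included in the co-morbidity groups |
| Sample size, Other comorbidities | Yes | No, listed under that heading |

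Read with the usage of sections M and N, step 4 has no main effect for either factor and no interaction of either with treatment. Any difference between obese and non-obese patients in that model's predictions would reflect only their mix of the covariates it does contain. Read with the usage of Aim 3 and the sample-size section, both factors could fall under co-morbidity. The protocol does not settle which reading applies, so two analysts could fit different models.

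**Inputs for scale.** Sample size considerations gives an outcome risk of 2.4%, an antibiotic odds ratio of 0.69, and 0.83 as the smallest detectable interaction odds ratio. Taking 2.4% as the untreated risk is consistent with the protocol's own sample size. With p1 the treated risk and a treated share of 0.80:

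- p1: odds 0.024/0.976 = 0.02459; × 0.69 = 0.01697; p1 = 0.016684.
- N = (1.960 + 0.842)² × [1/(0.20 × 0.024 × 0.976) + 1/(0.80 × 0.016684 × 0.983316)] / ln(0.69)² ≈ 7.849 × 289.65 / 0.13769 ≈ 16,511, against 16,512 stated.

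The 0.80 was solved for, since the main text does not give it. No sample size is in dispute here.

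**NNT by obesity.** NNT = 1/(untreated risk − treated risk). The effect of obesity on baseline odds is not in the protocol, so I assume a range of 1 to 2.

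- Non-obese: 1/(0.024 − 0.016684) = 136.7.
- Obese, baseline OR 1.5, with interaction 0.83: untreated odds 0.02459 × 1.5 = 0.03689, risk 0.03557; treated odds 0.03689 × 0.69 × 0.83 = 0.02112, risk 0.02069; NNT = 1/0.01489 = 67.2.

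| Assumed baseline OR for obesity | NNT in obese, no interaction | NNT in obese, interaction 0.83 |
|---|---|---|
| 1 | 137 | 99 |
| 1.25 | 111 | 80 |
| 1.5 | 93 | 67 |
| 2 | 71 | 51 |

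Both omitted terms matter. With no interaction at all, the main effect of obesity alone moves the NNT from 137 to 93 at a baseline OR of 1.5. Step 4 itself notes that NNTs can differ through background risk when the relative effect is similar.

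**Is stratification a way round?** I used one simulated cohort of 2 million, with assumed values: 25% obese, 65% of obese and 55% of non-obese treated, baseline OR 1.5, interaction 0.83. A crude comparison ignoring obesity gave one NNT of 117. Stratifying gave 139 in the non-obese (true 137) and 66 in the obese (true 67). Stratified analysis can therefore recover the subgroup NNTs.

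**The case against.** A reader might infer that NNTs by obesity and smoking cannot be derived at all, or that these two groups will have no Objective 4 result. The protocol does not support that. The Technical Summary says the rate and NNT analyses will be stratified by each listed characteristic, including obesity and smoking. Study Design closes by saying that results of every step will be stratified or adjusted by both. The section on comparison groups defines sub-groups by both for Objectives 1 to 4. The section on confounding proposes inverse probability weighting as a route to absolute risks and NNTs in different groups. The simulation confirms that such a route works in principle.

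Nor can one say that both factors will certainly go unadjusted. Section M lists them among the covariates to be included, and step 4 also adjusts for the probability of treatment. Which variables enter that propensity model is a detail that may properly sit in an analysis plan. It is also fair to say that co-morbidity sometimes includes both factors, in Aim 3 and in the sample-size text on this very interaction.

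These points narrow the defect without removing it. Stratified or adjusted is an either/or, and adjustment alone does not estimate effect modification. Separate stratum NNTs do not supply the interaction coefficient that step 4's significance rule needs, nor a ranking for step 5. Nor is this merely detail left for later: step 4 fixes an explicit list, and the list conflicts with the objective it serves.

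**Conclusion.** The point holds as an inconsistent specification of the Objective 4 model. As written, step 4 omits obesity and smoking status from its adjustment set and its interactions. It therefore does not test the stated hypothesis for them, cannot apply its interaction rule to them, and leaves their order of entry in Objective 5 undefined. It does not make the subgroup NNTs unobtainable.

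The conclusion rests on reading co-morbidity in step 4 as sections M and N otherwise use it. On the wider reading the omission disappears, but the ambiguity that allows both readings remains. The size is illustrative only: under the protocol's risk and odds ratios, an NNT of 137 in the reference group against 51 to 137 in obese patients, depending on the assumed baseline odds ratio (1 to 2) and on whether an interaction of 0.83 exists. The protocol gives no estimate of the obesity or smoking effect, so the true difference is unknown.

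**What to change.** In section N, step 4:

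1. Add obesity and smoking status to the adjustment set.
2. State that interactions of antibiotic treatment with age, co-morbidity, obesity and smoking status will be assessed.
3. Report NNTs by obesity and by smoking status.
4. State once, for the whole protocol, whether co-morbidity includes obesity and smoking, and use the term that way throughout. This also settles what the sensitivity analysis on the total number of co-morbidities in section M will count.

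Interactions with gender and SES, which Study Type also lists, may be considered but are not needed to resolve this point.

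The cost is a sentence or two and a few model terms. Both variables are already listed covariates, and the section on missing data covers BMI and smoking. There are more tests: with binary coding, two further interactions in each of six outcomes and three syndromes give up to 2 × 6 × 3 = 36 coefficients, more if smoking has several levels. They should be read with that number in mind. The change should be made before Objective 4 is run; the Amendments section reports only steps 1 and 2 as done.
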